### Statistics and sample size

Assuming an alpha error of α = 5%, a correlation between pre and post-intervention values of the Short Physical Performance Battery (SPPB) of ρ = 0.5 and a standard deviation for the SPPB of σ = 2.5, the required sample size to have a power of 90% to detect a minimum difference of 1 point between groups in the post–pre SPPB score is 101 patients per group. Taking into account an expected loss of patients along the follow-up of 15%, the final sample size required is 120 per group. For the estimation, an ANCOVA method for the analysis of the differences has been considered. The research team will be focused to instruct and remind geriatricians periodically to assess inclusion and exclusion criteria in all three centres in order to reach target sample size. All of the centres have a remarkable clinical activity attending around 1000 patients every year. It is expected than 15% of these patients in every centre can be potentially eligible participants. In the unlikely case of not reaching the expected sample size, we will extend the inclusion period for a further 3 months.

The description of the sample by group will be conducted using statistics such as means and standard deviations or medians and interquartile ranges for the quantitative variables, and frequencies and percentages for the qualitative variables. For comparisons between groups at baseline, *t* tests or Mann–Whitney *U* tests will be used for continuous variables, depending on normality, which will be checked for each using the Kolmogorov–Smirnov test and normal probability plots, and the chi-square test or Fisher’s test will be used for categorical variables. To determine the efficacy of the intervention in the quantitative variables, such as the SPPB, we will use ANCOVA models, using post-intervention values as dependent variables, group study as the principal effect and pre-intervention values as covariates. In the case of qualitative or categorized variables (such as whether an improvement of a given magnitude between pre and post intervention has been achieved or not), comparisons between groups will be conducted with the chi-square test or Fisher’s test, and complemented with logistic regression if additional adjustment is needed. The level of statistical significance will be 0.05. Data will be analysed using an intention-to-treat approach with R and SPSS statistical packages.

We will adopt a complete case analysis as the primary analysis if the proportions of missing data are equal to or below 5% and it is implausible that certain patient groups specifically are lost to follow-up in one of the compared groups. To check the assumption that the potential impact of missing data is negligible (created by a missing complete at random or a missing not at random mechanism), best–worst and worst–best case sensitivity analyses will be used. When the proportions of missing data are above 5% and if this is supported by the previous sensitivity analysis, a missing at random mechanism will be assumed and missing values will be imputed using the R package MICE (Multivariate Imputation via Chained Equations). If the proportions of missing data are very large (more than 40%) on important variables, then trial results will be considered as hypothesis-generating results.

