Frailty according to the Fried criteria	X			
Montreal Cognitive Assessment (MOCA)—only for mild cognitive impairment	X		X	X
Categorical scale of pain		X		X
Geriatric Depression Scale of Savage (GDS)		X		X
Minimental Cognitive Exam (MEC-Lobo)		X	X	X
Gait velocity test (GVT)		X	X	X
Dual task (verbal and counting GVT)		X	X	X
Maximal isometric force of handgrip, knee extension and hip flexion		X	X	X
Isaacs Set Test		X		X
Quality of Life (EQ-5D)		X		X
Trail Making Test (TMT—Part A)		X	X	X
1RM (leg press)		X	X	X
Muscle power at 50% 1RM in leg press		X	X	X
Drugs, geriatric syndromes and psycho-behavioural symptoms		X		X
Cumulative Illness Rating Scale for Geriatrics (CIRS-G)		X		
Functional Activities Questionnaire (FAQ)		X	X	X
Mini Nutritional Assessment (MNA)		X		
Acceleration data: gait kinematic parameters (regularity, variability, cadence), Five Times Sit to Stand Test (peak power, impulse) and balance parameters (power spectrum, area)		X	X	X
Rate and risk of falls		X	X	X
Mortality		X	X	X
Admission and readmission to hospital		X	X	X
Institutionalization		X	X	X

Basic sociodemographic data of the participants will be collected in the baseline visit. All adverse events, including those related to exercise such as muscle pain, fatigue and general aches and pains, will be recorded in an “adverse events diary” during follow-up visits and telephone calls by the training and testing staff, and by self-report during the study period. The study flow diagram is shown in Fig. 2. The time at which different variables (primary and secondary) will be measured is presented in Table 1. The protocol employs relevant standard protocol items for clinical trials according to the SPIRIT 2013 statement (Additional file 1) [29] and follows the CONSORT statement [30] for transparent reporting. The trial is registered at ClinicalTrials.gov (identifier number iNCT03657940), and the status is recruitment.

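### Falls are listed as a rate, but neither of the two stated analysis routes uses follow-up time; a count model with a person-time offset is a cheap, minor improvement to this secondary outcome

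*Protocol article*

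**What the plan says.** Table 1 (Study design and setting) includes "Rate and risk of falls" among the secondary outcomes, marked at baseline, 1 month and 3 months. The article gives no counting window or time unit for it.

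Statistics and sample size offers two routes for comparing the groups on outcomes:

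- Quantitative variables, with the SPPB as the example: "we will use ANCOVA models, using post-intervention values as dependent variables, group study as the principal effect and pre-intervention values as covariates".
- Qualitative or categorized variables: chi-square or Fisher's test, with logistic regression if adjustment is needed.

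No count model, rate model or exposure term appears. The same section plans for attrition ("Taking into account an expected loss of patients along the follow-up of 15" per cent) and for analysis by intention to treat. Complete cases are primary only if no more than 5% of data are missing and selective loss is implausible. Above 5%, if the sensitivity analyses support it, missing values are imputed by chained equations under missing at random.

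Adverse events are recorded separately, at visits, by telephone and by self-report.

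**The concern.** A fall rate is a number of events divided by time at risk. It is quantitative, so the general rule sends it to an ANCOVA of the value after the intervention. That model treats it as a score read at a visit. Two consequences follow if the rule is applied literally.

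- A patient who falls and then leaves before 3 months has no 3-month value. Complete-case analysis discards the falls already observed. Imputation fills in the absent value but does not count those falls as data. Imputation can draw on earlier visits, but it rests on missing at random, which is least secure when the fall itself leads to the loss.
- The 3-month value could be a count for months 1 to 3 or for the whole period. On the first reading, month-1 falls drop out of the comparison as well.

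The result would also be a difference in mean counts, although Table 1 calls the outcome a rate. The categorical route, which suits the risk half of the item, has no follow-up time either. At stake is information on one secondary outcome.

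**Working it through.** **The plan's own figure.** The only stated calculation is for the SPPB. Inputs from Statistics and sample size: "the required sample size to have a power of 90% to detect a minimum difference of 1 point between groups", "a standard deviation for the SPPB of σ = 2.5" and "correlation between pre and post-intervention values of the Short Physical Performance Battery (SPPB) of ρ = 0.5", with α = 5% taken as two-sided. By ANCOVA:

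n = 2σ²(1 − ρ²)(z₀.₉₇₅ + z₀.₉₀)²/δ² = 2 × 6.25 × 0.75 × (1.960 + 1.282)²/1² = 98.5, so 99 per group.

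A noncentral-t calculation gives 100, against 101 stated. Allowing for 15% loss, 101/0.85 = 118.8, so 119 against 120 stated. The figure reproduces. No fall rate, dispersion or effect is given, so there is no falls figure to reproduce and everything below rests on assumptions.

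**Share of observed falls used.** Assume 120 per arm, 3 months (0.25 years), 15% lost uniformly over follow-up, a constant rate of 1 per person-year and no group difference.

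- Observed falls: 2 × 120 × 0.25 × (1 − 0.15/2) = 55.5.
- Completers, months 0–3: 2 × 120 × 0.25 × 0.85 = 51.0. Unused: 4.5/55.5 = 8.1%.
- Completers, months 1–3 only: 51.0 × 2/3 = 34.0. Unused: 21.5/55.5 = 38.7%.

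The percentages do not depend on the rate. If losses occur uniformly between 0.1 and 3 months (mean 1.55), the cumulative share used is 2.55/(2.55 + 0.15 × 1.55) = 2.55/2.7825 = 91.6%, so 8.4% is unused. The interval share is 1.70/2.7825 = 61%.

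**Power.** Assumptions: Poisson counts with gamma frailty of shape 1, 120 per arm, 15% loss unrelated to falling, 500 simulations per cell. The Monte Carlo standard error is at most √(0.25/500) = 2.2 points. Entries are power in % at 1/2/3 falls per person-year.

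| Scenario | ANCOVA, completers, months 1–3 | ANCOVA, completers, months 0–3 | Negative binomial, all falls, offset |
|---|---|---|---|
| Constant rate ratio 1.7 | 37/60/73 | 49/74/85 | 53/79/88 |
| Constant rate ratio 0.6 | 24/38/55 | 29/51/67 | 30/55/72 |
| Rate ratio 2.0 in month 1 only | 7.0/5.8/5.0 | 15/24/33 | 19/31/40 |

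The offset model gains 4/5/3, 1/4/5 and 4/7/7 points over the cumulative ANCOVA. Given the simulation error, this is about 0–7 points. Over the interval ANCOVA the gains are 16/19/15, 6/17/17 and 12/25/35 points. Under no effect, every method rejects in 4–6% of runs.

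A second simulation (600 runs, rate ratio 0.5) used an overdispersed Poisson model with the same kind of offset. Power for interval ANCOVA, cumulative ANCOVA and offset model was 0.37, 0.48 and 0.51 at 1 fall per person-year, and 0.57, 0.72 and 0.77 at 2. Type I error was about 0.04 to 0.07.

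**Limits.** Both simulations analyse completers for the ANCOVA and do not run multiple imputation, which the expected 15% loss points to. In both, loss is unrelated to falling. They show lost information and say nothing about bias from falls that cause dropout.

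**The case against.** The article never names ANCOVA for falls. The sentence is a general rule with a scored scale as its example, and the model for one secondary count is a detail that a condensed article may leave to a fuller document. This carries weight, and it is why the point is minor. It does not remove the point: the article sets a rule for quantitative variables as a class, and that rule does not suit an outcome that its own table calls a rate.

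Four stronger readings are tempting, and the documents do not support them.

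- *Falls are the trial's main harm or benefit outcome.* They are one row of a long secondary list, and the abstract's secondary endpoints omit them. Fewer falls is part of the rationale for this type of exercise.
- *Month-1 falls will be left out.* That needs an interval count, which is not stated. The programme lasts 12 weeks, Table 1 also marks falls at 1 month, and a cumulative count fits the text equally well.
- *Falls before dropout will be deleted.* Complete cases are primary only up to 5% missing, and the expected loss is 15%. Imputation is the likelier route, although it does not count the observed falls either.
- *An early excess of falls would go unseen as a harm.* Adverse events are recorded separately, and nothing sends the safety review through ANCOVA.

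**Conclusion.** The point holds as a minor improvement to one secondary outcome. Neither stated route uses follow-up time, so under a literal reading falls seen before dropout do not enter the comparison directly. With a cumulative count the cost is about 8–9% of observed falls and about 0–7 points of power. With an interval count it is about 39% of falls and a larger loss of power, but that window would have to be assumed.

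These sizes rest on assumed rates of 1–3 falls per person-year, gamma shape 1, 15% loss unrelated to falling, and ANCOVA in completers. Type I error stays near 5% throughout, so the demonstrated cost is precision, not a false-positive risk. Leaving the window open also allows it to be chosen after the data are seen.

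**What to change.** In Statistics and sample size, exclude falls from the ANCOVA rule and state:

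*The number of falls from randomization to 3 months or last contact will be compared between groups by negative binomial regression, with log follow-up time as offset and baseline falls as covariate, in all randomized patients with any follow-up. The rate ratio and its 95% confidence interval will be reported.*

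Rate ratios for months 0–1 and 1–3 are optional. They will be imprecise and should be labelled descriptive.

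The cost is a short addition to the text and a standard model in R, which the plan already uses. It needs fall counts from the scheduled contacts and the dates of visits, dropout and death. The downside is that the estimate becomes a rate ratio instead of a mean difference. No trial procedure changes.

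### No ordinal method is named for the categorical pain scale; if it has three or more ordered levels and is tested as an unordered table, the order is ignored and power against a consistent shift falls

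*Protocol article*

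**What the plan says.** The protocol article, under Statistics and sample size, gives two routes for efficacy.

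- **Quantitative outcomes:** "To determine the efficacy of the intervention in the quantitative variables, such as the SPPB, we will use ANCOVA models", with the pre-intervention value as covariate.
- **Qualitative or categorized outcomes:** "comparisons between groups will be conducted with the chi-square test or Fisher’s test, and complemented with logistic regression if additional adjustment is needed". The example attached to this rule is "such as whether an improvement of a given magnitude between pre and post intervention has been achieved or not".

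The only rank method in the section concerns baseline: "For comparisons between groups at baseline, *t* tests or Mann–Whitney *U* tests will be used for continuous variables". The description of the sample by group uses "frequencies and percentages for the qualitative variables".

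Table 1 (Study design and setting) places a "Categorical scale of pain" in the secondary outcomes block, marked at baseline and at 3 months. The article does not give its number of levels, their wording, an expected effect or a power for it, and the statistics section does not mention pain.

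**The concern.** By the article's own label, the pain scale belongs to the second route. A pain scale is in all likelihood ordered, although the article does not say so. On a table with more than two levels, Pearson's chi-square and the r × c Fisher test give the same result however the levels are permuted. A shift of the whole distribution towards less (or more) pain is then spread over K − 1 degrees of freedom instead of being concentrated in one.

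Two things follow:

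- A real, consistent shift is more likely to be missed.
- The test itself supplies no directed effect estimate with a confidence interval.

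The two routes also treat baseline differently. ANCOVA adjusts for the baseline value as a matter of course. The categorical route does so only if logistic regression is added, although baseline pain is collected.

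**Working it through.** **1. The plan's own figure.** The only sample size stated is for the SPPB. Inputs from Statistics and sample size: difference 1, SD 2.5, pre-post correlation 0.5, alpha 0.05 (taken as two-sided), power 90%.

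n per group = 2 × (1.960 + 1.282)² × 2.5² × (1 − 0.5²) / 1² ≈ 98.5, so 99. A t-based calculation gives 100. The article states 101, which agrees within rounding. With 15% loss, 101 / 0.85 = 118.8, so 119 against the stated 120. This figure is sound. It also sets the scale for pain: about 101 evaluable per arm (120 × 0.85 = 102).

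**2. Cost of ignoring order, analytically.** Assumptions, because the article gives none for pain: K ordered levels, an effect that is a consistent shift, two-sided 5%, and an ordered 1-df test with 80% power. The noncentrality that gives this power is

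λ = (1.960 + 0.842)² ≈ 7.85.

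The unordered test has power P[χ²(K − 1, λ) > c], where c is the 95% point of the central χ² on K − 1 df.

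| Levels K | df | c | Power of unordered test | Loss from 80% (points) |
|---|---|---|---|---|
| 2 | 1 | 3.84 | 80.0% | 0 |
| 3 | 2 | 5.99 | 70.9% | 9.1 |
| 4 | 3 | 7.81 | 64.5% | 15.5 |
| 5 | 4 | 9.49 | 59.5% | 20.5 |
| 6 | 5 | 11.07 | 55.5% | 24.5 |

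If the ordered test has 90% power instead, the losses for 3, 4, 5 and 6 levels are 6.5, 11.6, 16.0 and 19.7 points.

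**3. Check by simulation.** 20,000 trials per scenario, 101 per arm, proportional-odds shift, Pearson chi-square against the tie-corrected Mann–Whitney test. At an assumed common odds ratio of 2.0:

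| Assumed control distribution | Chi-square | Mann–Whitney |
|---|---|---|
| 3 levels, equal | 65.2% | 75.0% |
| 3 levels, 50/30/20 | 60.2% | 70.8% |
| 4 levels, equal | 61.8% | 77.6% |
| 4 levels, 40/30/20/10 | 57.8% | 74.5% |
| 5 levels, equal | 57.5% | 78.7% |
| 5 levels, 35/25/20/13/7 | 54.8% | 76.4% |

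Over odds ratios of 1.5 to 2.2 the loss is about 7 to 11 points with 3 levels, 12 to 17 with 4 and 15 to 22 with 5. With no effect, both tests reject at about 5%, so the chi-square test is valid; what it loses is efficiency.

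**4. When the effect is not a consistent shift.** Four levels, control 40/30/20/10, same sample size:

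- The top level falls from 10% to 2% and only the level below it gains (20% to 28%): chi-square 59%, Mann–Whitney 6%.
- The lowest level rises from 40% to 55%, all from the next level (30% to 15%): chi-square 62%, Mann–Whitney 28%.

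So the ordered test is not better in every case.

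**The case against.** The strongest reply is that the article never says pain will be tested as a multi-level table. The one example under the categorical rule is binary, and with two levels no order is lost in the test. This stands as a limit: the power figures apply only to a scale of three or more ordered levels tested as such. It does not remove the point, because the example only illustrates the rule and no cut-point is given for pain. Splitting the scale would bring a cost of its own.

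Second, pain is a minor outcome. It appears in one row of Table 1 and not in the abstract's endpoints or the outcome text. The same block of the table holds items measured only at screening or baseline, so listing there does not prove that a hypothesis test is planned. Pain is, however, measured again at 3 months. This bears on importance and is reflected in the verdict.

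Third, the detailed model for one secondary scale may be left to an analysis plan that is not shown. The point here is narrower: the article already states a rule for categorical outcomes, and that rule suits an ordered scale poorly.

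Some stronger readings are tempting but unsupported:

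- **That the plan gives no direction for pain at all.** Percentages by group are planned for qualitative variables, and logistic regression, if used, gives a directed odds ratio. The gap is in the multi-level test itself.
- **That the logistic supplement forces a cut into two levels.** The article says only logistic regression, without specifying binary.
- **That exercise-related muscle pain could be missed.** Those events are recorded in an adverse events diary, not on this scale, and do not depend on this test.

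**Conclusion.** The point holds in conditional form. The stated rule for categorical outcomes does not use the order of the pain scale, names no ordinal alternative for efficacy, and adjusts for baseline pain only as an option. With 3, 4 or 5 ordered levels tested as an unordered table, power against a consistent shift falls from an assumed 80% to 70.9%, 64.5% or 59.5%.

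A reader might take the resulting 9 to 21 points as this trial's loss of power. The article does not support that, since it gives no number of levels, distribution, effect or power for pain. Across 2 to 6 levels and benchmarks of 80% to 90%, the loss runs from 0 to about 25 points, and it can turn into a gain for chi-square when the change is confined to adjacent levels.

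No bias or inflation of type I error arises, and the SPPB analysis and sample size are untouched. This is a cheap improvement to one secondary outcome.

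**What to change.** In Statistics and sample size, limit the chi-square and Fisher rule to binary and truly unordered variables. Add that the categorical pain scale at 3 months is analysed on its full set of ordered levels by a proportional-odds (ordinal logistic) model, with group as the main effect and the baseline pain category as covariate. Report the common odds ratio with its 95% confidence interval, beside the table of pain categories by group.

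The cost is one sentence in the analysis section. Pain is already collected at both times, so no data, visits or patients are added. The downside is small: the model assumes a roughly common shift across levels and can miss a change confined to one part of the scale, which is why the category table should be shown with it.

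### Pre/post responder outcomes get an unadjusted chi-square or Fisher test, with baseline adjustment left to an undefined need, although the same paragraph adjusts quantitative outcomes for baseline

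*Protocol article*

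**What the plan says.** All of the relevant text is in the protocol article, Statistics and sample size.

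- **Quantitative outcomes, the SPPB included:** ANCOVA with the post-intervention value as dependent variable, group as the main effect and the pre-intervention value as covariate. The sample size assumes the same method.
- **Qualitative or categorised outcomes:** the example given is "whether an improvement of a given magnitude between pre and post intervention has been achieved or not". Groups are compared by chi-square or Fisher's test, "complemented with logistic regression if additional adjustment is needed". The article does not say what would make adjustment necessary or what would be adjusted for.
- **Level:** "The level of statistical significance will be 0.05".

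No responder outcome is named as primary. The abstract makes change in the SPPB the primary endpoint, with 1 point as clinically significant, and gives 5 points for the Barthel Index.

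**The concern.** The chance of gaining at least 1 SPPB point depends on where the patient starts. With a pre/post correlation of 0.5, low starters tend to drift up and high starters down. The scale stops at 12 (Outcome measures, Primary outcome), so a patient near the top has little room to gain. The plan conditions on the starting value when the SPPB is analysed as a score and stops doing so when the same SPPB is analysed as a yes/no gain. It gives no reason for the difference.

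Two things are at stake. First, the responder comparison has less power than the data already collected would allow. Second, because the condition for adjusting is undefined, the decision can be taken after both results are known.

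**Working it through.** **Inputs from Statistics and sample size.** "Assuming an alpha error of α = 5"% (sidedness not stated; two-sided assumed); correlation, "SPPB) of ρ = 0.5"; "standard deviation for the SPPB of σ = 2.5"; target, "power of 90% to detect a minimum difference of 1 point between groups in the post–pre SPPB score is 101 patients per group".

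**Assumptions not in the article.** Responder means a gain of at least 1 SPPB point. Pre and post scores are bivariate normal, then rounded and bounded to 0–12. The baseline mean is 6.5, 8 or 9.

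**Step 1: the plan's own figure.** ANCOVA sample size per group:

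n = 2(1.960 + 1.282)² × σ²(1 − ρ²) / δ² = 2 × 10.51 × (6.25 × 0.75) / 1² = 98.5, so 99. The t-based solution is 99.5, so 100.

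The article states 101, which agrees closely; power at 101 is 90.7%. For 15% loss, 101 / 0.85 = 118.8, so 119 against the stated 120. The sample size stands.

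**Step 2: the same effect as a responder outcome, before rounding or ceiling.** The SD of change is σ√(2(1 − ρ)) = 2.5 × √1 = 2.5.

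- Control: P(gain ≥ 1) = 1 − Φ(1/2.5) = 1 − Φ(0.4) = 34.5%
- Intervention: P(gain ≥ 1) = 1 − Φ(0) = 50.0%

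A two-proportion test at 101 per group has 61% power; 90% would need 211 per group. On whole-number scores, a gain of 1 corresponds roughly to 0.5 on the underlying scale. That gives 42.1% against 57.9% and 62% power, so the picture is the same.

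**Step 3: what conditioning on baseline recovers.** Simulation, 101 per arm, baseline mean 6.5, 10,000 trials per scenario. Chi-square is without continuity correction; the logistic model contains group and baseline SPPB.

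| ρ | Power, chi-square | Power, logistic | Gain (points) | Power, ANCOVA on the score |
|---|---|---|---|---|
| 0.3 | 49.6% | 56.7% | 7.1 | 82.9% |
| 0.5 | 62.7% | 68.5% | 5.8 | 89.3% |
| 0.7 | 83.4% | 85.6% | 2.2 | 97.6% |

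At ρ = 0.5 the continuity-corrected chi-square has 57.4% power.

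Varying the assumed baseline mean at ρ = 0.5:

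| Baseline mean | Chi-square | Logistic | Gain (points) |
|---|---|---|---|
| 6.5 | 64% | 70% | 6 |
| 8 | 59% | 66% | 7 |
| 9 | 52% | 61% | 9 |

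A repeat with 3,000 trials per scenario gave 64% and 70%, 60% and 67%, and 51% and 62%: gains of 6, 7 and 11 points. The gain grows as more patients start near the ceiling.

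**Step 4: type I error (no effect, mean 6.5).** At ρ = 0.5, chi-square rejects in 5.6% of trials and adjusted logistic regression in 5.1%. Over ρ = 0.3 to 0.7 the ranges are 4.8–5.7% and 4.6–5.1%. Taking whichever p-value is smaller gives 7.6% at ρ = 0.5 and 6.1–7.8% over ρ = 0.7 to 0.3. The repeat at ρ = 0.5 gave 7.2–7.9%.

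**The case against.** The strongest reply is that little depends on this. The responder comparison appears only as an example of a categorised variable, and the trial was not sized for it. The primary SPPB analysis already conditions on baseline. The chi-square test is valid, and the article's wording makes logistic regression an addition to it rather than a substitute, so reporting the smaller p-value is not something the text invites. Most of the shortfall from ANCOVA comes from dichotomising: at ρ = 0.5 and mean 6.5 the gap is 89.3 − 62.7 = 26.6 points, of which adjustment recovers 5.8. All of this stands, and it limits the weight of the point. It does not explain why one outcome is treated in two ways, or when adjustment would count as needed.

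Two stronger readings are tempting but not supported.

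- **That baseline significance tests would choose the covariates.** The paragraph does plan such tests ("tests will be used for continuous variables, depending on normality", with chi-square or Fisher's test for categorical variables), but as part of comparing the groups at baseline. It never links their results to adjustment. Even under that rule, adjusting only when baseline SPPB differed at p < 0.05 gave type I error of 5.0% and power of 63.4% (ρ = 0.5, mean 6.5): no inflation, and almost none of the available gain.
- **That baseline information is thrown away.** The baseline value is part of the definition of a gain. What is lost is conditioning on it.

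The lack of a covariate list or a numerical cut-off in that sentence is not a fault either. An analysis plan that is not shown may supply them, and the abstract already gives 1 point for the SPPB and 5 for the Barthel Index.

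**Conclusion.** The point holds as a minor one about supportive analyses. The plan fixes a valid but less efficient test for pre/post responder outcomes and leaves the better analysis to an undefined condition. For a gain of at least 1 SPPB point at the planning values, the cost is about 6 to 10 points of power over assumed baseline means of 6.5 to 9. At mean 6.5 it ranges from about 2 points (ρ = 0.7) to 7 points (ρ = 0.3). The type I error of about 7% to 8% is a worst case that the wording fails to exclude; it is not a prediction of what the investigators would do.

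These figures assume a two-sided 5% test, the 1-point cut-off, and normal scores rounded and bounded to 0–12. A reader might infer that the trial's main result is biased or underpowered. It is not: the primary ANCOVA and the 101 and 120 per group are untouched.

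**What to change.** In Statistics and sample size, make logistic regression with group and the outcome's own pre-intervention value the prespecified analysis for every pre/post responder variable. Keep chi-square or Fisher's test only for categorical outcomes with no baseline value, such as death during follow-up. Delete the clause that makes adjustment conditional. How the effect is expressed, and any further covariates, can be left to the analysis plan.

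The cost is wording only. Table 1 already schedules the pre-intervention SPPB at baseline and the Barthel Index at screening, so no visit, measurement or patient is added.

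### Above 5% missing data, imputation under missing at random depends on a best–worst case analysis that cannot assess that assumption, with no stated criterion and no fallback

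*Protocol article*

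**What the plan says.** All the relevant text is in the Protocol article, under Statistics and sample size.

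- **Model and population.** Quantitative outcomes such as the SPPB are compared by ANCOVA on the post-intervention value, adjusted for the pre-intervention value. "Data will be analysed using an intention-to-treat approach".
- **Expected loss.** The sample size allows for an "expected loss of patients along the follow-up of 15" per cent.
- **5% missing or less.** Complete cases are primary, provided that selective loss of particular patients from one arm is implausible.
- **Sensitivity analysis.** Best–worst and worst–best analyses are to check the assumption that missing data have negligible potential impact. A parenthesis describes that impact as "created by a missing complete at random or a missing not at random mechanism".
- **More than 5% missing.** "When the proportions of missing data are above 5% and if this is supported by the previous sensitivity analysis, a missing at random mechanism" is assumed, and MICE is used.
- **More than 40% missing on important variables.** Results are treated as hypothesis-generating.

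**The concern.** The rule selects the primary analysis, and its middle branch covers the loss that the trial expects. Three features make that branch unsafe.

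1. Best–worst and worst–best analyses fill missing values with favourable values in one arm and unfavourable values in the other. They show how much missing data could matter. They hold no information on why the values are missing, so they can neither support nor refute MAR.
2. It is unclear what has to be supported or what result would count as support. If support is absent, no analysis is named for missingness above 5%.
3. The condition is evaluated on outcome results by arm, so the handling of lost participants is settled after those results are known. That sits badly with a pre-specified intention-to-treat comparison.

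A separate wording problem is that the parenthesis puts missing not at random (MNAR) beside missing completely at random (MCAR) in a phrase about negligible impact. The impact of MNAR data is the one that cannot be presumed negligible.

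At stake is who chooses between complete-case and imputed results for the primary SPPB comparison, and when.

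**Working it through.** **Inputs from the Protocol article, Statistics and sample size**
- "Assuming an alpha error of α = 5" per cent (two-sided assumed; sidedness is not stated)
- "a correlation between pre and post-intervention values of the Short Physical Performance Battery (SPPB) of ρ = 0.5"
- "a standard deviation for the SPPB of σ = 2.5"
- "power of 90% to detect a minimum difference of 1 point between groups in the post–pre SPPB score is 101 patients per group"
- 15% loss, 120 per group

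From Primary outcome: the SPPB runs from 0 to 12.

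**Step 1: reproduce the plan's sample size.** The ANCOVA residual SD is 2.5 × √(1 − 0.5²) = 2.165. The normal approximation gives n = 2 × (1.960 + 1.282)² × 2.165² / 1² ≈ 98.5, so 99 per group. With the t distribution, power is 90.2% at 100 and 90.4% at 101. Allowing for loss, 101 / 0.85 = 118.8, so 119 against 120 stated. The plan's figures reproduce within rounding, so its inputs can be used for the rest.

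**Step 2: which branch applies.** 15% lies above 5% and below 40%, so the expected case is the conditional branch. 15% of 120 is 18 participants per arm.

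**Step 3: how wide the bounds are at 15% loss.** The article gives no extreme values, so three rules are assumed. Best–worst means favourable values in the intervention arm and unfavourable values in the control arm; worst–best is the reverse. Loss is equal in both arms and the true effect is 1 point.
- Arm mean ±1 SD: 1 ± 0.15 × 2 × 2.5 = 1.75 and 0.25
- Arm mean ±2 SD: 1 ± 0.15 × 2 × 2 × 2.5 = 2.5 and −0.5
- Scale ends: 0.85 × 1 ± 0.15 × 12 = 2.65 and −0.95

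**Step 4: how often the three analyses agree under MCAR.** Trials were simulated with 120 per arm, 18 per arm missing completely at random, SD 2.5, correlation 0.5, assumed mean SPPB of 8 and ANCOVA at 0.05, with 600 runs per cell. Agreement means that complete-case, best–worst and worst–best give the same conclusion.

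At a 1-point effect the simulated mean estimates (best–worst, worst–best) were 1.75 and 0.25 (±1 SD), 2.47 and −0.52 (±2 SD), and 2.58 and −1.02 (scale ends). The small gap from the formula at the scale ends arises because simulated scores were cut to 0–12, which lowers the complete-case effect to 0.92: 0.85 × 0.92 ± 1.8 = 2.58 and −1.02.

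Agreement at 15% loss:

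| True effect | ±1 SD | ±2 SD | Scale ends |
|---|---|---|---|
| 0 | 0% | 0% | 0% |
| 1 point | 15% | 0% | 0% |
| 1.5 points | 71% | 2% | 0% |
| 2 points | 98% | 26% | 0% |

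Even at 5% loss and a 1-point effect, agreement was 77%, 36% and 6%.

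The missingness mechanism is MCAR in every cell. Agreement still moves from 0% to 98%, driven by the effect size and the extreme values chosen. The check therefore responds to quantities other than the one it is asked to judge.

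**Step 5: the two readings of the condition.**
- *Reading A: MAR is supported if the extreme cases agree with the main result.* At 15% loss and the design effect the condition usually fails, and no analysis is then named.
- *Reading B: imputation is supported if the extreme cases show that the impact is not negligible.* Wide bounds then trigger MICE, and no analysis is named above 5% when the impact is negligible.

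Both readings leave a gap, and they send the same data in opposite directions.

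**The case against.** The strongest reply is that nothing forces Reading A. The sentence before the condition says that the extreme cases test whether missing data matter. It is natural to continue that, above 5%, where they do matter, one imputes. The wide bounds in step 3 would then start MICE, not block it. This stands: a reader might infer that the condition is bound to fail at 15% loss, and the text does not support that. Even on Reading A, failure depends on extreme values and an agreement criterion that the article does not give.

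A reader might also infer that the expected scenario has no valid primary analysis. That goes too far. The article names ANCOVA, an intention-to-treat approach and MICE under MAR; what it lacks is a usable trigger and a fallback.

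Nor does the parenthesis assert that MNAR data are harmless. Negligible impact is the assumption being tested, and extreme-case bounds are a legitimate way to gauge how much MNAR could matter. The phrase is badly worded, no more.

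Unequal loss between arms is plausible in an exercise trial, but no figure in the article documents it, and the complete-case branch does take selective loss into account.

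Finally, imputation covariates and the definition of the extreme values may properly sit in a fuller plan that is not shown. Their absence is not criticised here. The point concerns a decision rule that the article does state.

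**Conclusion.** The concern holds in this form: the stated trigger for MAR imputation is ambiguous, rests on an analysis that cannot assess MAR, is evaluated on outcome results by arm, and has no fallback. It governs the primary SPPB comparison at the loss the plan itself expects.

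The size depends on the reading. On Reading A, with the design effect and MCAR data, the condition would be met in about 15% of trials at ±1 SD and in none of the simulated trials at ±2 SD or the scale ends; at ±1 SD it would be met in 98% if the true effect were 2 points. On Reading B, MICE would run wherever the bounds are judged wide. The extreme-value rules, the agreement criterion, equal loss by arm and the mean SPPB of 8 are assumptions. That the bounds cannot identify the mechanism depends on none of them.

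This should be fixed. It does not undermine the planned ANCOVA or the choice of MICE.

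**What to change.** - Delete the clause that makes imputation depend on the preceding sensitivity analysis.
- State that the baseline-adjusted ANCOVA with MICE under MAR is the primary analysis whenever missing data exceed 5%. Applying it at any level of missingness would be simpler still, but is optional.
- Keep best–worst and worst–best as descriptive bounds that select nothing, and state the values used.
- Add a delta-adjusted (tipping-point) sensitivity analysis for MNAR, showing how far imputed values would have to shift before the conclusion changes.
- Reword the parenthesis so that MNAR is not grouped with MCAR as a mechanism of negligible impact.

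The cost is a wording change and a few hours of extra analysis, since MICE is already planned. The change should be made before any outcome results are seen by arm.
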